Despite the emergence of varied needs following discharge, there is often limited communication, lack of coordinated and continuous professional support as the burn patient transits from hospital to the home/community [13, 14, 19]. Home care and support may become chaotic, often with limited access to professional support. Some burn survivors may not also return to the hospital for follow-up care due to long travel distances and associated costs. Comprehensive follow-up system of care in the home/community is therefore greatly needed to promote rehabilitation of burn survivors [20]. It is worth mentioning that the home/community has been identified as a suitable location for the implementation of burn rehabilitation programmes which can enhance patient outcomes, particularly if the programme is structured and have active follow-ups on the burn survivor [21].

In Mainland China, the concept of burns rehabilitation is new to some provinces [22], and only in recent years that rehabilitation of the burn patient was considered an integral part in the Chinese burn care system [23]. Where available, it has been observed that significant challenges exist which include lack of hospital support with no standardised rehabilitation guidelines, inadequate rehabilitation knowledge among practitioners, human resource shortages, limited funding, and financial burden on the burn patients [24]. The rehabilitation protocols, if available, usually focus primarily on the physical aspects of the injury which leaves limited room to attend to the psychosocial concerns of the patient recovering from burns [25]. Consequently, burn patients may not have adequate rehabilitative care as inpatients and with limited support following discharge which adversely affects their recovery process. Thus, to bridge the immediate pre-discharge and early post-discharge gap aiming to improve patient outcomes, a nurse-led transitional burns rehabilitation programme (4Cs-TBuRP) has been developed following the Medical Research Council (MRC) Framework [26] (see Fig. 1, a tentative logic model underpinning the intervention).

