## Trial design

The trial is a double-arm (intervention and control groups), single-centre randomised controlled trial with 1:1 allocation ratio and a follow-up process evaluation phase. We will firstly undertake a pilot feasibility phase and follow-up with the full-scale trial. The null hypothesis is that there will be no difference regarding outcomes between the intervention and control groups. The alternative hypothesis is that there will be statistically significant differences between the participants undergoing the nurse-led programme of care and participants receiving the existing standard of care.

The follow-up process evaluation phase will employ a multi-method approach (qualitative and quantitative strands) to examine the process and issues during the implementation process [34]. Twelve process measures covering domains such as recruitment, follow-up, intervention delivery, and data collection will be considered in the process evaluation phase (see Table 1). The qualitative strand will capture changes in the implementation process and experiences with the intervention from the perspectives of adult burn survivors and nurse case managers. The quantitative strand will offer insight into key process variables such as recruitment, follow-up, and adherence rates. Details regarding the process evaluation phase (process measures, variables, methods, and participants) are provided in Table 1.

**Table 1 Tab1:** Outline of process evaluation for the nurse-led transitional rehabilitation program

Process measures	Process variables	Method	Participants and data collection method
Recruitment and selection rate	• Number of burn survivors screened at the study setting. • Number of participants from the sample of eligible persons. • Number of participants versus aimed number	Enrolment record review	Site manager (research team member)/data collection team
Barriers and facilitators in recruitment and selection process	• Motivation of participating eligible persons. • Experience with recruitment and selection	Semi-structured interviews	Adult burn survivors Recruiting nurses
Follow-up and attrition rate	• Number of participants completing follow-up	Follow-up record review	Site manager (research team member)/data collection team
Barriers and facilitators for follow-up	• Reasons for drop-out • Motivation for continued participation	Semi-structured interviews	Adult burn survivors

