Quality of delivery of the interventional components	• The part of each component and the complete intervention delivered by nurse case managers • Satisfaction with delivery	Semi-structured interviews	Nurse case managers
Barriers and facilitators for delivery of interventional components	• Reasons for deviating from, or applying components as planned	Semi-structured interviews	Nurse case managers
Adherence to interventional components	• Number of sessions followed • Intervention components fully implemented and rationale • Intervention components partly implemented and rationale • Intervention components not implemented and rationale • Compliance to individual recommendations	Semi-structured interviews	Adult burn survivors and nurse case managers
Barriers and facilitators for adherence to interventional components	• Motivation for (or lack of) compliance	Semi-structured interviews	Adult burn survivors and nurse case managers
Experience of participants and nurse case managers with the components of the nurse-led interventions and training programme for the nurses.	• Perceived benefit v actual benefit • Strong and weak aspects of the interventional components (structure and content) • Experiences with the educational component (adequacy in assisting burn care nurses to deliver the intervention)	Semi-structured interviews	Adult burn survivors (in intervention group) and nurse case managers
Experience of participants with clinical outcomes associated with the intervention.		Semi-structured interviews	Adult burn survivors (in intervention group)
Completeness of data collection	• Reasons why data were missing • Reasons why participants were excluded from analysis	Semi-structured interviews	Data collection team
Barriers and facilitators for data collection		Semi-structured interviews	Data collection team

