### Eligibility criteria

All burn survivors receiving burn care services at the study site will be screened for eligibility during the study period. Adult burn survivors aged ≥ 18 years with burn size ≥ 10% TBSA as assessed by the burn surgeon/burn care nurse (irrespective of the depth of the burn), absence of a confirmed psychiatry condition, renal failure, or diabetes mellitus and reachable on phone and WeChat will be considered for inclusion. Adult burn survivors who are unable to communicate or are enrolled in another rehabilitation trial will be excluded. Drop out will be ascertained based on participants exiting either the control or intervention before the 12th week with no intention to continue their participation. Participants for the follow-up process evaluation phase will be recruited from both arms of the trial. The intervention will be primarily provided and coordinated by two burn care nurses with referrals to other members of the multi-disciplinary burns team which comprises of burn surgeons, rehabilitation medicine specialist, and social worker/psychologist who are involved in caring for burn patients at the study site. These burn care nurses recruited to deliver the intervention will have at least 4 years working experience in the burn unit at the study site and must complete a mandatory training programme which covers contents of the comprehensive transitional care program for burn patients with theory and practice (18 h in total) and passed a competence test prior to participating in the study. Other nurses working in the same unit provide routine care to all patients and are not involved in the intervention. Since most of the nurses working in the unit are not involved with the intervention cases, the risk of contamination is minimal.

The objectives of the mandatory training programme were to enable the burn care nurses to be able to master the concept of transitional care; assess, manage, and monitor the transitional needs of burn patients using the Omaha System and make referral when applicable and demonstrate burns rehabilitation competencies (comprehensive scar, itch, and pain management; psychosocial care; aromatherapy; exercises and splinting; monitoring nutrition and hydration; and infection prevention). See Table 2 for details regarding the training programme.

**Table 2 Tab2:** Details of training programme for burn care nurses based on the TIDieR checklist

TIDieR checklist					

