### Sampling and sample size estimation

Subjects will include adult burn survivors with burn size ≥ 10% TBSA from the Burn Unit. Upon recruitment, randomisation to either control or treatment group (ratio 1:1) with a blinded approach will be carried out. For the pilot phase of the project, the pilot feasibility sample size rule suggested by Whitehead, Julius, Cooper, & Campbell will be used [50]. The rule specifies that a total sample size of 25 participants per arm. Considering possible attrition rate of 20% that has been reported in burn care literature implies that an additional 5 participants will be added to both arms summing up to 30 participants per arm (total = 60 participants).

For the main trial, the sample size calculation based on the primary outcome measure (Burn Specific Health Scale) at 95% confidence level, 90% statistical power and moderate effect size will yield a total of 38 participants per arm [51–53]. Considering an attrition rate of 20%, the final sample size will be 45 participants per arm (total = 90 participants). In all, 150 participants will be recruited for the entire study. For the follow-up process evaluation phase, we will conveniently recruit up to fifteen [15] participants from each arm whilst being guided by the principle of data saturation in addition to the burn care nurses delivering the intervention to complete the qualitative strand. Data saturation will be determined at the point where no new data emerges. The quantitative strand will include review of the recruitment, enrolment, and follow-up records.

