### Recruitment

A research nurse at the study site will identify potential subjects’ eligibility for enrolment in the study based on the inclusion and exclusion criteria described above. All participants will be enrolled/recruited by a Registered Nurse (RN-1) who will not be involved in the delivery of the intervention or outcome assessment (see Fig. 3). RN-1 will follow-up on patient’s case notes on daily basis to ascertain if any adult burn survivor has a pending discharge status. If pending discharge is noted, RN-1 will check if the adult burn survivor fulfils the criteria for inclusion; if so, the patient will be invited to participate. Details of the study will be made known and information sheet duly explained. Thereafter, RN-1 will ensure that two consent forms (covering both outcome and process evaluation phases) are signed or thumb printed by the adult burn survivor which will then be forwarded to a research assistant (RA) who will complete the baseline assessment. A research team member (RTM) who is not involved in clinical services and have no knowledge about the potential subjects will take over from this phase and proceed to work on randomisation and allocation. The subjects allocated to the intervention arm will be referred to the nurse case manager to commence the intervention. Following the exit of participants from the intervention, they will be contacted and invited to participate in the process evaluation phase.

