## Data collection, management, and analysis

### Data collection methods and management

All outcomes will be assessed at baseline (T0); that is after the patient has been recruited. Following the completion of the intervention, the second phase of data collection (T1) will be undertaken; that is at the 8th week. The third phase of data collection (T2) will be the follow-up phase at 4 weeks post-intervention. Data collection will be in the form of completion of questionnaires. The data collection process will be undertaken by three research assistants who will be blinded to the groups of the participants. The research assistants have completed a 10-h training programme covering the outcome measures to be used. Following the training, they undertook a role play to enable the research team to ascertain the inter-rater reliability/percentage agreement with the following results: Burn Specific Health Scale-B (87.7%), EQ-5D-5L (100%), HADS (92.5%), PSQI (86.7%), DASH (84.4%), VAS (100%), BPI (100%), and VSS (100%). All quantitative data will be entered and stored in SPSS Version 25 (SPSS, an IBM company, Chicago, Illinois, USA). All hard copies of documents relating to the study will be stored under lock and key only accessible to designated research team member.

For the follow-up process evaluation phase (qualitative strand), face to face semi-structured interviews with an interview guide will be utilised to collect data after the intervention period has elapsed. Topics for the interview guide will be based on the process evaluation components as highlighted in Table 1. All interview proceedings will be audiotaped and transcribed verbatim in the Trint Automated Transcription Software. Interview transcripts will be exported to QSR NVivo version 10 will be used to manage the data. All soft files related to the study will be kept in a password protected computer only accessible to the principal investigator and the doctoral student investigator. Paper files will be kept under lock and key. For the quantitative phase, we will review the recruitment, enrolment, and follow-up records.

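### Convenience recruitment and face-to-face-only interviews risk under-representing drop-outs, although survivor interviews are the only listed method for reasons for drop-out

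*Protocol article*

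**What the plan says.** All references are to the protocol article.

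- **Who is interviewed.** Under Sampling and sample size estimation: "we will conveniently recruit up to fifteen [15] participants from each arm whilst being guided by the principle of data saturation". The burn care nurses who deliver the intervention are interviewed as well.
- **How and when.** Under Data collection methods and management: "face to face semi-structured interviews with an interview guide will be utilised to collect data after the intervention period has elapsed". No interview place and no remote alternative are given.
- **Invitation.** Under Recruitment: "Following the exit of participants from the intervention, they will be contacted and invited to participate in the process evaluation phase". Consent covering the process evaluation is taken at enrolment.
- **What the interviews must deliver.** In Table 1 (Trial design), the row on barriers and facilitators for follow-up lists "Reasons for drop-out • Motivation for continued participation". Its only method is the semi-structured interview and its only source is adult burn survivors. A further row lists "Motivation for (or lack of) compliance", with both survivors and nurse case managers as sources.
- **Who counts as a drop-out.** Under Eligibility criteria: someone who leaves either arm before week 12 and does not mean to carry on.
- **What the reasons are for.** The Discussion names drop-out as an anticipated limitation. Its answer to attrition bias is to examine how much drop-out there is, and why, in the two groups.
- **Access.** Background and rationale: "Some burn survivors may not also return to the hospital for follow-up care due to long travel distances and associated costs". Eligibility requires that participants be reachable remotely: "reachable on phone and WeChat will be considered for inclusion".

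**The concern.** The sampling rule and the purpose pull in different directions. Reasons for leaving have to come from survivors, and the most direct informants are those who left. By the protocol's own definition these people have decided not to continue, so a rule that takes whoever is conveniently available is the one least likely to reach them. Requiring a meeting in person may add a second filter in the same direction for patients who live far away.

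The saturation principle does not repair this. Saturation is reached when interviews stop yielding new material, and that can happen among completers alone without a single drop-out having been heard.

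At stake is the secondary objective on implementation issues, and the explanation of attrition that the Discussion promises. Reasons for leaving could be thinly documented or missing in one arm, and the reported experience of the programme could look more favourable than it was.

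**Working it through.** The cap of 15 per arm is guided by saturation and has no formula behind it, so there is no figure of the plan to reproduce. The check has two parts.

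**1. Sources for each topic, side by side**

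| Topic | Sources in the article |
|---|---|
| Number completing follow-up | Follow-up record review |
| Reasons for drop-out | Survivor interviews only |
| Lack of compliance | Survivor and nurse case manager interviews; also contact records, care-plan review and nurse diaries (fidelity section) |
| Reasons for missing data or exclusion from analysis | Interviews with the data collection team |

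Record review gives the extent of drop-out. The reasons, as the patient sees them, have one listed route.

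**2. How many drop-outs would be interviewed**

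Inputs from the article: attrition 20%; 45 participants per arm in the main trial; 15 interviewees per arm at most. Assumed input: *r*, the chance that a drop-out is recruited to interview relative to a completer. The article gives no value for *r*.

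- Drop-outs per arm: 0.20 × 45 = 9.
- Representative sample: expected drop-outs among 15 = 15 × 9/45 = 3.0. The chance that a random 15 of 45 contains none is C(36,15)/C(45,15) = 1.6%. If the pool is the whole study (15 drop-outs among 75 per arm), the mean is again 3.0 and the chance of none is 2.3%.
- Convenience sample: share of drop-outs *p* = 0.2*r*/(0.2*r* + 0.8); expected number = 15*p*; chance of none = (1 − *p*)^15, a binomial approximation.

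| *r* (assumed) | *p* | Expected drop-outs per arm | Chance of none in an arm |
|---|---|---|---|
| 1 | 0.200 | 3.0 | 3.5% |
| 0.5 | 0.1/0.9 = 0.111 | 1.7 | 17% |
| 0.25 | 0.05/0.85 = 0.059 | 0.9 | 40% |
| 0.1 | 0.02/0.82 = 0.024 | 0.4 | 69% |
| 0 | 0 | 0 | 100% |

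At *r* = 1 the binomial gives 3.5% where the exact draw from 45 gives 1.6%, so the last column slightly overstates the chance of none.

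The Discussion needs reasons from both groups. Treating the arms as independent, the chance that at least one arm has no drop-out interviewed is 1 − (1 − 0.171)² = 31% at *r* = 0.5 and 1 − (1 − 0.403)² = 64% at *r* = 0.25.

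**The case against.** The strongest reply is that much of the worry is prediction.

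- A reader might infer that the design selects completers. The text does not say so. Invitations follow exit from the intervention, and the drop-out definition also speaks of exiting, so exit need not mean completion. Drop-out reasons are a named interview topic, so drop-outs are among the intended interviewees, and they have already consented to this phase.
- A reader might infer that only patients able to travel are interviewed. The article gives a mode, not a place. Home visits are already part of the programme, and home interviews are not ruled out.
- A reader might infer that the programme is aimed at patients who cannot return to hospital. The Background says only that some may not return, and eligibility sets no such condition.
- Non-adherence does not depend on survivor interviews alone, and the data collection team is asked why data are missing. The Discussion does not say that its examination of drop-out rests on the 15 interviewees per arm.
- The size depends on an assumed *r*, and a saturation-guided sample does not aim at proportional representation.

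All of this stands as a limit on the claim. What it does not remove is that the article itself fixes convenience recruitment and the face-to-face mode, lists survivor interviews as the only method for reasons for drop-out, and sets neither a minimum number of drop-outs nor a remote option. These are stated choices, not details left to a fuller document.

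**Conclusion.** The point holds as a mismatch between a stated sampling rule and a stated purpose. The risk is under-representation of drop-outs and, less certainly, of distant patients; exclusion of either group is not written into the plan. The gap lies mainly in reasons for drop-out.

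The size is conditional. The benchmark of 3 drop-outs per arm rests on the protocol's 20% attrition and a full 15 interviews. The fall to about 1.7 or 0.9 rests on drop-outs being recruited at one half or one quarter of the completers' rate, which the documents neither support nor contradict. With equal availability nothing is lost.

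The primary effect estimate, the randomisation and the outcome comparisons are unaffected. This is an inexpensive improvement to a secondary objective and to the account of attrition, not a flaw in the trial's main inference.

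**What to change.** 1. In Sampling and sample size estimation, replace convenience recruitment with purposive sampling by completion and adherence status, within the same cap of 15 per arm. Reserve some places in each arm for early leavers and low adherers; the exact number is for the team to set. Judge saturation with these participants included.
2. In Data collection methods and management, allow interviews by telephone or WeChat as well as face to face. The eligibility criteria already require participants to be reachable on both.

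The cost is a change of protocol wording. The maximum number of interviews is unchanged. The small downside is that remote interviews may be less rich than those held in person.

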### Recruitment

A research nurse at the study site will identify potential subjects’ eligibility for enrolment in the study based on the inclusion and exclusion criteria described above. All participants will be enrolled/recruited by a Registered Nurse (RN-1) who will not be involved in the delivery of the intervention or outcome assessment (see Fig. 3). RN-1 will follow-up on patient’s case notes on daily basis to ascertain if any adult burn survivor has a pending discharge status. If pending discharge is noted, RN-1 will check if the adult burn survivor fulfils the criteria for inclusion; if so, the patient will be invited to participate. Details of the study will be made known and information sheet duly explained. Thereafter, RN-1 will ensure that two consent forms (covering both outcome and process evaluation phases) are signed or thumb printed by the adult burn survivor which will then be forwarded to a research assistant (RA) who will complete the baseline assessment. A research team member (RTM) who is not involved in clinical services and have no knowledge about the potential subjects will take over from this phase and proceed to work on randomisation and allocation. The subjects allocated to the intervention arm will be referred to the nurse case manager to commence the intervention. Following the exit of participants from the intervention, they will be contacted and invited to participate in the process evaluation phase.

**Fig. 3 Fig3:**
[figure not shown]
Work flowchart

